**Figure 1 figure1:**
[figure not shown]
Inclusion and exclusion criteria flowchart. The T-branch group is patients referred to the emergency room with mild or moderate forms of COVID-19 not requiring hospitalization. The D-branch group is patients referred to the emergency room with severe or critical forms of COVID-19 requiring hospitalization.

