### Clinical Assessment Protocol

The clinical evaluation aims to identify the signs and symptoms associated with COVID-19 and monitor the status (mild/moderate or severe/critical) of the disease. Clinical assessments include identification of comorbidities, COVID-19–associated symptoms and treatment, use of medications in general, clinical chemistry findings, and life support regimen care. Severe cases are defined for the purposes of the study by dyspnea (respiratory rate >30 breaths per minute) coupled with any of the following criteria: pulsed wave oxygen saturation <93% at rest, PaO_2_/FiO_2_ ≤300 mmHg, respiratory failure requiring mechanical ventilation, multiple organ failure, shock, or admission to the intensive care unit. Patients who do not meet the criteria for severe/critical forms will be considered mild/moderate cases. No asymptomatic patients will be included (Textbox 1 and Table 1).

Components being assessed for characterization of the following domains: symptoms, comorbidities, treatments, biochemical profile, immune biomarkers, and leukocyte phenotype and functionality in the TARGET protocol.

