### Timeline

The TARGET protocol comprises two arms, referred to as the timeline (T)-branch and the days of hospitalization (D)-branch. For the purposes of this study, the T-branch refers to patients with mild/moderate forms that did not require hospitalization. The D-branch refers to patients with severe/critical forms who required hospital admission. Patients on the T-branch will be analyzed on days 0, 9, and 18 (T0, T9, and T18), while patients on the D-branch will be analyzed on days 0, 3, 9, and 18 (D0, D3, D9, and D18; Figure 1).

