### Statistical Analysis

Clinical and demographic data between groups of patients (severe vs nonsevere) as well as treatment profiles and differences in successive time points will be compared. To compare mean values of soluble biomarkers between groups, the *t* student test (or analysis of variance with post hoc test for multiple groups) or the nonparametric Mann-Whitney (or Kruskal-Wallis for multiple groups) test will be used as appropriate, according to the observed sample distribution features. The SAS 9.3 software (SAS Institute Inc) will be used with a significance level set at .05. The main binary outcomes will be analyzed by the estimation of relative risks using a log-binomial generalized model or by the area under the curve using trapezoidal methods. All personnel conducting laboratory procedures will be blinded regarding the patient status (severity of COVID-19). Receiver operating characteristic curves will determine cutoff points at which individual or combined scores of the molecular and cellular biomarkers become informative of the progression of COVID-19 cases, according to optimal sensitivity and specificity to identify the signature that best characterize each clinical status.

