## Discussion

This TARGET protocol was designed to standardize the evaluation of cellular and molecular immune biomarkers to evaluate their potential as prognosis tools during COVID-19 infection at different degrees of clinical severity. As the host immune response impacts COVID-19 progression, understanding the behavior of immune biomarkers at the different phases of the illness constitutes a crucial step in the identification of patients who will deteriorate and those who will benefit most from treatment. A simultaneous comprehensive assessment of the different aspects of the immune response was the approach adopted for this protocol.

An early study in China showed that the elevation of certain biomarkers such as D-dimer, together with inflammatory markers including ferritin, was associated with the worst outcomes after SARS-CoV-2 infection [33]. These measurements have been incorporated in some clinical practice centers, but their course during disease and actual value in prognosis are not yet fully described. Higher levels of a series of other interleukins were also described in severe forms of the disease [34], contributing to the concept of a cytokine storm, but their exact significance remains unclear. A thorough evaluation of different immune aspects could help to clarify their role.

Less information regarding the cellular immune response has been published, but its role is progressively gaining more attention from the scientific community, as some evidence notes that humoral immunity does not appear to be sufficiently developed after the first SARS-CoV-2 infection [35]. A simultaneous evaluation of these two kinds of immune responses in the TARGET study could help to understand this interface.

Thromboembolism is a recurrent finding among patients with COVID-19, which has made thromboprophylaxis a vital part of the available supportive treatment options. Unfortunately, there is considerable uncertainty about the degree of coagulation derangement, the possible association with the inflammatory response elicited including neutrophil extracellular traps [36], and the consequences of these alterations [13]. Further knowledge is needed to better understand COVID-19–associated coagulopathy to provide frontline clinicians with better treatment options to manage the ensuing clinical manifestations.

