In summary, TARGET is a translational study that aims to verify the role of cellular and molecular immune biomarkers in the prognosis of COVID-19, opening up avenues for their use in clinical practice. The results that will be achieved are not meant to be restricted to the description of the disease pathophysiology, but to form a basis for future clinical studies that will ultimately help the clinicians on the front line.

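### The ROC cutoffs are claimed to inform progression, but their stated criterion is the severity that already defines the branches at entry, so they show discrimination of current status and do not by themselves support prognosis

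*Protocol article*

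**What the plan says.** The Discussion gives the study a prognostic purpose. The protocol was designed to standardize biomarker evaluation and "to evaluate their potential as prognosis tools during COVID-19 infection at different degrees of clinical severity". Understanding the markers is presented as a step towards "identification of patients who will deteriorate". The closing summary says that TARGET "aims to verify the role of cellular and molecular immune biomarkers in the prognosis of COVID-19".

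The Statistical Analysis section names one analysis for cutoffs: ROC curves for individual or combined biomarker scores that "become informative of the progression of COVID-19 cases, according to optimal sensitivity and specificity to identify the signature that best characterize each clinical status". Separately, it says: "The main binary outcomes will be analyzed by the estimation of relative risks using a log-binomial generalized model". Those outcomes are not named.

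Status is defined under Clinical Assessment Protocol, where the clinical evaluation is to "monitor the status (mild/moderate or severe/critical) of the disease". The Figure 1 legend fixes the branches at presentation: "The D-branch group is patients referred to the emergency room with severe or critical forms of COVID-19 requiring hospitalization". The T-branch is the mild or moderate counterpart, and under Timeline "the T-branch refers to patients with mild/moderate forms that did not require hospitalization". Biological Samples places the first blood sample at inclusion. Table 1 records supplementary oxygen, mechanical ventilation and death at days 0, 3, 9 and 18.

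**The concern.** One sentence promises information about progression and then sets a criterion that is not progression. A ROC curve answers the question posed by its reference standard. If that standard is mild/moderate versus severe/critical disease, and every patient was placed in a branch by it before or at the first sample, the curve describes the marker as a correlate of existing severity. A good AUC there may reflect consequences of severe disease or of its treatment. It does not show that a raised value in a patient who is still stable precedes worsening.

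At stake is the main clinical message. A cutoff chosen to separate the two branches could be reported as a tool for spotting patients who will deteriorate, although no patient's later course entered its derivation.

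**Working it through.** **1. The ROC target, traced through the text.**
- Claimed use: progression (Statistical Analysis) and prognosis (Discussion).
- Stated criterion: the signature of each clinical status (Statistical Analysis).
- Status: mild/moderate or severe/critical (Clinical Assessment Protocol).
- When it sorts patients: at emergency-room referral (Figure 1 legend).
- First marker sample: day 0, at inclusion (Biological Samples).

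The reference standard is therefore the grouping variable, and it does not come after the marker. Re-assessing status at later visits does not change this if a day-9 marker is set against day-9 status. The comparison is still concurrent. No stated analysis pairs an earlier marker with a later event.

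**2. Why the label matters if severity is modelled as the outcome.** The plan gives no AUC, event rate or precision target for the ROC, so it has no figure of its own to reproduce here. Sample Size Calculation assumes elevated TNF-α in 20% of critically ill and 5% of noncritically ill patients, at a ratio of 1. Results reports 85 D-branch and 30 T-branch patients at the end of July 2020. With Ns severe and Nm mild patients, put a = 0.20·Ns, b = 0.05·Nm, c = 0.80·Ns, d = 0.95·Nm. Then PPV = a/(a+b), RR = [a/(a+b)]/[c/(c+d)] and OR = ad/(bc).

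| Mix (severe:mild) | PPV | Risk if not elevated | RR | OR |
|---|---|---|---|---|
| 100:100 (planned ratio) | 20/25 = 0.80 | 80/175 = 0.457 | 1.75 | 4.75 |
| 85:30 (interim) | 17/18.5 = 0.92 | 68/96.5 = 0.705 | 1.30 | 4.75 |
| 5:95 (assumed) | 1/5.75 = 0.17 | 4/94.25 = 0.042 | 4.10 | 4.75 |

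The marker is the same in all three rows. RR and PPV follow the recruitment mix, and the odds ratio does not.

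**3. What a prognostic analysis would cost in precision.** Assumptions: AUC (A) = 0.75, 100 patients per branch, Hanley-McNeil standard error. Q1 = A/(2−A) = 0.600 and Q2 = 2A²/(1+A) = 0.643. SE² = [A(1−A) + (n1−1)(Q1−A²) + (n2−1)(Q2−A²)]/(n1·n2), where n1 have the event and n2 do not.
- Severity contrast, 100 vs 100: SE 0.034, 95% half-width 0.07.
- Within one branch, 5% deteriorate (5 vs 95): SE 0.129, half-width 0.25.
- 10% (10 vs 90): SE 0.092, half-width 0.18.
- 20% (20 vs 80): SE 0.067, half-width 0.13.
- 30% (30 vs 70): SE 0.057, half-width 0.11.

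The article gives no deterioration rate, so the range stands in for one.

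**The case against.** The strongest reply is that this is a prospective cohort. Status is monitored, successive time points are compared, and outcomes are recorded to day 18. The word progression could then be read as meaning follow-up status. The Objective in the Abstract is only to compare mild and severe forms, which a status ROC serves well. The prognostic language sits in the Discussion and is tempered there: the results are to form a basis for future clinical studies. Outcome definitions and time horizons may be in the full protocol or an analysis plan.

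Much of this stands. It limits the point to the criterion that the ROC sentence itself states. That criterion is written down, so it is not a detail left to another document, and it does not match the use claimed for it.

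A reader might infer more than the text supports:
- *That the relative risks also target severity at entry.* The article never names the main binary outcomes. They could be death or ventilation. The table above applies only if severity is modelled as the outcome. In the direction used for the sample size (elevated TNF-α given severity) the ratio is 20/5 = 4 at any mix.
- *That the study cannot show prediction.* This is true of the branch contrast, not of the cohort.
- *That the T-branch is selected on its future course.* This rests on the past tense of one verb under Timeline. The Figure 1 legend fixes the branch at referral, and the Figure 2 legend says only that the prospectively followed group will primarily evolve mildly. Nothing says that patients who worsen are moved or dropped.
- *That the AUC is inflated by comparing outpatients with intensive-care patients.* Intensive-care admission is only one of several alternative criteria for severe disease, and the documents allow no estimate of such inflation.

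**Conclusion.** The point holds for the ROC analysis. As written, its cutoffs discriminate severity already present, and they cannot on their own carry the prognostic conclusion drawn in the Discussion. This rests on the wording of the ROC criterion, the definition of status and the timing of the first sample, and on no assumed figure.

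The numbers are illustrations. If severity were the modelled outcome, RR would be 1.75 at the planned mix, 1.30 at the interim mix and 4.10 if 5% of cases were severe (assumed), with PPV of 80%, 92% and 17% and an odds ratio of 4.75 throughout. Whether any relative risk in the plan is affected depends on outcomes that the article does not name. The change should be made, because the claim and the stated analysis do not match and the follow-up needed to match them is already planned.

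**What to change.** 1. Label the severe-versus-nonsevere ROC as discrimination of current status. If severity is ever modelled as the outcome, report odds ratios, because RR and PPV depend on the recruitment mix.
2. For any statement about progression or prognosis, keep each patient in the day-0 branch. Relate markers to a later event recorded in Table 1 by day 18, for example new supplementary oxygen, new mechanical ventilation or death. Analyse within branch, among patients free of that event when the marker is sampled. For markers first measured on day 9 (D-dimer, thromboelastometry, neutrophil assays), use a landmark at day 9 and events after it.
3. If this is not done, limit the conclusion to association with severity.

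First meeting the study's severe criteria, or being admitted, would be a natural event for the T-branch. It cannot be built from Table 1 alone, which lists neither hospital admission, respiratory rate nor PaO2/FiO2.

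Cost: with the events named in item 2, the change is to the analysis wording and needs no new visits. Results says that analysis was to start after inclusion data were collected, although the coagulation branch is already being analysed and would need the relabelling now. The price is fewer events per branch, wider intervals and a more modest claim.

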## Results

This protocol is in the data collection phase. Study recruitment started in June 2020. At the end of July 2020, 30 T-branch and 85 D-branch patients were enrolled.

We expected to complete all patient inclusion by June 2020, but with the continuous increase in COVID-19 cases in Brazil, the authors decided to continue including patients until February 2021.

Data analysis is scheduled to start after all inclusion data have been collected.

The coagulation study branch, with thromboelastometry, has already been completed. Preliminary results confirm deregulation in initiation of the hemostasis process. The results are currently being analyzed and prepared for publication.

## Discussion

This TARGET protocol was designed to standardize the evaluation of cellular and molecular immune biomarkers to evaluate their potential as prognosis tools during COVID-19 infection at different degrees of clinical severity. As the host immune response impacts COVID-19 progression, understanding the behavior of immune biomarkers at the different phases of the illness constitutes a crucial step in the identification of patients who will deteriorate and those who will benefit most from treatment. A simultaneous comprehensive assessment of the different aspects of the immune response was the approach adopted for this protocol.

An early study in China showed that the elevation of certain biomarkers such as D-dimer, together with inflammatory markers including ferritin, was associated with the worst outcomes after SARS-CoV-2 infection [33]. These measurements have been incorporated in some clinical practice centers, but their course during disease and actual value in prognosis are not yet fully described. Higher levels of a series of other interleukins were also described in severe forms of the disease [34], contributing to the concept of a cytokine storm, but their exact significance remains unclear. A thorough evaluation of different immune aspects could help to clarify their role.

Less information regarding the cellular immune response has been published, but its role is progressively gaining more attention from the scientific community, as some evidence notes that humoral immunity does not appear to be sufficiently developed after the first SARS-CoV-2 infection [35]. A simultaneous evaluation of these two kinds of immune responses in the TARGET study could help to understand this interface.

Thromboembolism is a recurrent finding among patients with COVID-19, which has made thromboprophylaxis a vital part of the available supportive treatment options. Unfortunately, there is considerable uncertainty about the degree of coagulation derangement, the possible association with the inflammatory response elicited including neutrophil extracellular traps [36], and the consequences of these alterations [13]. Further knowledge is needed to better understand COVID-19–associated coagulopathy to provide frontline clinicians with better treatment options to manage the ensuing clinical manifestations.

A metabolomics study of serum from patients with COVID-19 annotated 941 metabolites. The authors identified metabolic patterns in severe cases that could be used to propose diagnostic models capable of predicting progression to severe infection and assist in the treatment strategy [37]. Observed changes in the lipid profile (>100 lipids) cause liver damage, as reflected by abnormal serum levels of bilirubin and bile acids [37]. Another study revealed the consequences of treating patients with SARS-CoV with methylprednisolone. Disturbances in the serum lipid profile 12 years post infection were associated with long-term systemic damage caused by high doses of methylprednisolone [38]. Metabolomics is therefore a powerful tool for identifying and monitoring the prognosis and markers at different stages of a disease, particularly for unknown infections [24].

Similarly, neutrophil functional and molecular assays have been performed in patients with COVID-19 [39], clearly indicating the participation of these cells in the pathogeny, although no specific molecular model has yet been proposed [40]. Therefore, the proteomic approach coupled with further analysis at the transcription and functional level will provide evidence to correlate neutrophil activity to the disease severity and time course.

Only two treatments have shown substantial beneficial effects to date in randomized trials in COVID-19, with both exhibiting heterogeneity of treatment effect between subgroups. A preliminary report from Beigel et al [41] showed that remdesivir shortened the median recovery in a trial from 15 days in the placebo group to 11 days, but those on mechanical ventilation were less likely to benefit. On the other hand, dexamethasone demonstrated a reduction in mortality at 28 days, but mainly in those on mechanical ventilation [42]. One possible explanation for these findings is that an adequate immune response to stop viral replication is needed at the onset of the disease. The excess of inflammation presenting is detrimental. As the time when these treatments are initiated could be key, immune biomarkers that signal phases of disease to guide the timing of treatments could be extremely useful in clinical practice.

In summary, TARGET is a translational study that aims to verify the role of cellular and molecular immune biomarkers in the prognosis of COVID-19, opening up avenues for their use in clinical practice. The results that will be achieved are not meant to be restricted to the description of the disease pathophysiology, but to form a basis for future clinical studies that will ultimately help the clinicians on the front line.

## Abbreviations

ACE2: angiotensin converting enzyme-2
CNPq: Conselho Nacional de Desenvolvimento Científico e Tecnológico
D: days of hospitalization
EXTEM: extrinsic system assay
FIBTEM: fibrinogen assay
IFN-γ: interferon-gamma
INTEM: intrinsic system assay
MCP-1: monocyte chemoattractant protein-1
NATEM: nonactivated coagulation assay
PBMC: peripheral blood mononuclear cells
PMA: phorbol 12-myristate 13-acetate
qRT-PCR: quantitative reverse transcription polymerase chain reaction
RECOVERY: Randomised Evaluation of COVID-19 Therapy
RT-PCR: reverse transcription polymerase chain reaction
SARS-CoV: severe acute respiratory syndrome–related coronavirus
STROBE: Strengthening the Reporting of Observational Studies in Epidemiology
T: timeline
TNF-α: tumor necrosis factor-alpha
UnB: University of Brasília
UPLC-PDA-QqTOF: ultra-performance liquid chromatography photodiode array quadrupole-quadrupole-time-of-flight
WHO: World Health Organization
